### Evaluation activities

All research participants and community research team members will be included in the evaluation. Intervention and control group participants will be given an online pretest near the start of participation and an online posttest after activities are completed, as well as a follow-up survey approximately one year after the posttest (Table 2). Community research team members at the three sites will receive the same pre-, post-, and follow-up surveys. Focus group participants will receive a brief pre- and posttest survey only. For a subset of analyses, we will compare responses by participant type (intervention and control group participants, community research team members, and focus group participants). The evaluation surveys are distinct from the surveys taken by the Delphi method and control group participants. The former are designed to assess changes in key outcome measures (i.e., mobilization, motivation, and participation) to assess the impact of participatory research approaches on civic engagement, while the latter ask participants to propose and prioritize strategies to address opioid misuse in their communities.

**Table 2 Tab2:** Evaluation data collection activities for RCT participants

	Pretest	Posttest	Follow-up
**Topic Group/** **Delphi Group – Intervention**	Demographic Survey Mobilization scale Community engagement survey Group dynamics (selected) Group readiness	Mobilization scale Community engagement survey Interview Group dynamics Process questions	Mobilization scale Community engagement survey Open ended responses
**Control**	Demographic Survey Mobilization scale Group readiness (selected)	Mobilization scale Process questions	Mobilization scale

A second outcome measure is strategy development (the number, type, and diversity of strategies created). To compare strategies across groups, members of the research team will code the strategies to indicate the focus, or domain, of each question. We will use the codes to calculate the number of domains addressed by each group and the number of domains (if any) that were unique to that group.

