**Methods:**

Two communities will use the SEED Method and one will use a modified Delphi method. We aim to recruit a total of 144 participants (48 per community). The evaluation team will randomize participants to an intervention group or a control group. In addition, we will collect outcome data from the participatory research team members leading the projects in each county (*n* = 18) and from additional community members who participate in focus groups (*n* = 32). The primary outcome for all participants will be the change in self-reported civic engagement as measured by the total score on the Individual Mobilization Scale.

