### Randomization

A member of the evaluation team will randomize when there are eight consented participants in a specific group. Each of the eight consented participants will be assigned a unique number from one to eight. Using the “Sequence Generator” from random.org, participants will be randomized to an intervention or control group. This process will be repeated until each intervention group/control group has the target number of participants.

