The control groups will be asked to develop a list of strategies like those developed in the intervention groups but without the participatory processes experienced in the SEED Method and Delphi groups. Control group participants in each county will receive two online surveys created by the evaluation team. The first survey will ask them to identify strategies, and the second survey will ask them to prioritize those strategies.

In sum, for the SEED Method, each Topic group will work independently and develop its own set of priority strategies, which will be combined for the action planning phase. For the Delphi method, all stakeholders will work together and develop one set of strategies. Control groups in each county will work separately, resulting in one set of strategies for each county.

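### The pretest appears to be completed after participants know their arm, so a reaction to assignment could enter the change score that is the primary outcome

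*Protocol article*

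**What the plan says.** All places are in the protocol article.

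- **Outcome.** Abstract, Methods: "The primary outcome for all participants will be the change in self-reported civic engagement", measured by the Mobilization Scale total.
- **Trigger for allocation.** Randomization: "A member of the evaluation team will randomize when there are eight consented participants in a specific group". Consent is the only condition named; no pretest is mentioned before this step.
- **Timing of the pretest.** Evaluation activities: "Intervention and control group participants will be given an online pretest near the start of participation and an online posttest after activities are completed".
- **Content of the pretest.** In Table 2 the intervention cell reads "Demographic Survey Mobilization scale Community engagement survey Group dynamics (selected) Group readiness". The control cell reads "Demographic Survey Mobilization scale Group readiness (selected", so controls get no Community engagement survey, no Group dynamics items and only part of Group readiness. The Mobilization Scale itself is listed for both arms at all three waves.
- **Timing of the posttest and follow-up.** The posttest comes once activities are over, and the follow-up about a year after it. Neither has a fixed date or interval.
- **Activities.** Under Implementation, SEED Topic groups have seven meetings. The Delphi group has an opening meeting, two surveys and a closing meeting. For controls, "Control group participants in each county will receive two online surveys created by the evaluation team".

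**The concern.** In an individually randomised trial the baseline is normally fixed before anyone can know the allocation. Here the sequence appears to be consent, allocation, then pretest. The arms cannot be blinded and they differ visibly: facilitated meetings against two online surveys and, under Participant compensation, a stipend of $250 against $70. Learning the assignment could move a self-rating of motivation, self-efficacy or participation in either direction before any activity has taken place.

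Two things are at stake. First, the pretest is one half of the primary outcome, so an arm-specific shift in it becomes part of the estimated effect. Second, Table 2 places the demographic survey inside the pretest. Someone who learns their arm and never completes the pretest leaves no baseline survey data, yet the Data analysis section relies on demographics and earlier data to explore drop-out and to support imputation.

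A lesser question is whether the posttest falls at the same time in both arms, given how much the activities differ.

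**Working it through.** **Order of events.** Set side by side, Randomization requires only eight consents, Evaluation activities places the pretest close to the start of participation, and Table 2 makes its content depend on the arm. An arm-specific form needs a known arm. The examples of group-dynamics items under Outcomes measures (members respecting and listening to one another) presuppose a group to belong to. Pretesting after allocation is therefore strongly implied, but not stated.

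**The plan's own yardstick.** Inputs from Sample size and power analysis (Tables 3 and 4): mean 1.87, SD 0.37, alpha 0.05, power 0.80, 3 × 24 = 72 per arm, stated minimum detectable difference (MDD) 0.12 (6.5%). The check takes alpha as two-sided, which the article does not state.

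MDD = SD × (z for alpha/2 + z for power) × √(2/n per arm)

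- 72 per arm: 0.37 × (1.960 + 0.842) × √(2/72) = 0.173.
- The stated value, 0.122 or 6.5% of 1.87, is returned by 144 per arm. It is also returned by 72 per arm if change is analysed with a pre-post correlation of r = 0.75: 0.173 × √(2 × (1 − 0.75)) = 0.122, with no inflation for clustering. The article gives no such correlation.

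So 0.173 is the yardstick used here. It is the value for a single-time score and also for a change score at r = 0.5, before any inflation for clustering.

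**Size of the bias.** If knowing the arm shifts one arm's pretest by b, the between-arm difference in mean change moves by the full b. The documents give no value for b, so these shifts are assumptions:

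| Assumed shift | Points | Share of 0.173 |
|---|---|---|
| 0.1 SD | 0.1 × 0.37 = 0.037 | 21% |
| 0.2 SD | 0.2 × 0.37 = 0.074 | 43% |

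The yardstick for a change score depends on r. At r = 0.3 it is 0.204 and the 0.1 SD shift is 18% of it; at r = 0.7 it is 0.134 and the share is 28%.

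**Effect on type I error.** Standard error of the difference in change = 0.37 × √(2(1 − r)) × √(2/72), with r assumed to be 0.5 to 0.7 and no clustering:

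| b (points) | Two-sided error, nominal 5% |
|---|---|
| 0.02 | 6% to 7% |
| 0.04 (about 0.1 SD) | 10% to 13% |
| 0.06 | 16% to 24% |

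Using the pretest as a covariate reduces the bias to about r × b but does not remove it. At b = 0.06 that is 0.030 to 0.042 points, with a type I error of 9% to 16%.

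**Timing.** No arm's duration or survey spacing is given, so a difference in elapsed time cannot be computed.

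**The case against.** The strongest reply is that the article nowhere says that the pretest follows allocation. Table 2 lists instruments by wave, not by sitting. The common scale could be completed at consent and the group items added once groups form. That is possible, and it is why the point is worded as an appearance. But nothing in the article describes such a split, and the only stated trigger for allocation is consent.

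A reader might go further in three ways that the documents do not support.

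- **Priming.** One might infer that the extra intervention-arm items colour the answers to the primary scale. Table 2 lists the Mobilization Scale ahead of those items, with only demographics, common to both arms, before it. Order of administration is not given. Priming is not shown.
- **Confounding with calendar time.** One might infer that each arm's posttest is tied to the end of its own activities. One sentence covers both arms and can equally mean a single date per county. Study timeline gives one shared calendar, and Data analysis models change over Years 1, 2 and 3, which also fits common waves. Seven meetings against two surveys is a difference in content, not evidence of different elapsed time. Exact survey windows may also sit in the full protocol.
- **A larger share.** Against the stated 0.12, the same shifts would be 31% and 62%. That yardstick does not follow from 72 per arm at SD 0.37 without an unstated correlation, so those shares should not be used.

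It is also fair to say that the plan intends to study predictors of drop-out and non-response, and that participants will know their arm at the posttest wherever the pretest is placed. Both stand. The first is weakened for people who skip the pretest, because their demographics are missing too. The second limits what the fix can achieve but does not justify an avoidable bias at baseline.

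**Conclusion.** The point holds as a design weakness that should be corrected. The baseline of a self-reported change outcome appears to be collected after participants know their arm. This rests on a strong inference from Table 2 and the Randomization section, not on an explicit statement.

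Neither the size nor the direction of any bias can be derived from the documents. The 0.037-point figure (21% of 0.173) shows only what an assumed 0.1 SD reaction would do, with 72 per arm and no clustering. Unequal posttest timing is a secondary matter: the text allows it but does not show it.

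**What to change.** Have all eight consented people complete one identical pretest (demographics, Mobilization Scale, items common to both arms) after consent and before their block is randomised. State this order under Randomization and under Evaluation activities. Give the intervention-only items (Community engagement survey, group dynamics, the remaining group readiness questions) as a separate form after allocation.

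Secondarily, send the posttest and the follow-up to both arms in the same calendar window within each county.

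The cost is small, since one evaluation team both randomises and runs the surveys. Each block may wait a short time for the last pretest, and a common window means that people who finish early wait for the rest of the county. The change protects the baseline only. Posttest and follow-up remain unblinded self-report, and the article should list that among its limitations.

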### Recruitment

Recruitment will occur through a combination of outreach strategies, including personal contacts, flyers and messages sent to partner organizations to be shared with potential participants, social media postings or advertisements, and advertisements in local media. The outreach materials will provide contact information for the study coordinator. The study coordinator will review eligibility criteria with potential participants and confirm eligibility for a specific stakeholder group within the relevant site. Once deemed eligible, the research coordinator will obtain informed consent. The target is 48 participants per county (144 total) divided as follows: 24 in the intervention group (For the SEED Method they are further divided into three stakeholder Topic groups) and 24 in the control group (composed of an equal number of stakeholders from each group). These are our target numbers, but flexibility will be allowed which may result in some stakeholder groups being larger or smaller than the target based on the community research teams’ ability to recruit.

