### Sample size and power analysis

**Table 3 Tab3:** Number of planned participants by site and intervention type

	Site 1 (SEED Method)	Site 2 (SEED Method)	Site 3 (Delphi method)
**Intervention**	24 (3 groups of 8)	24 (3 groups of 8)	24 (1 group, with number of specific stakeholder groups TBD)
**Control**	24	24	24

The power analysis is calculated based on the sample sizes of the intervention and control group participants only. A target number of 48 participants per community will be recruited and randomized to the intervention or control condition (24 per condition) (Table 3). Minimal detectable differences between the variables of primary interest were estimated with this sample size, setting the alpha error at 0.05 and the beta error at 0.20, adjusting for the estimated ICC and the usual population variances based on cited research (Table 4). Based on these analyses, the anticipated sample size will have an 80% probability of detecting treatment differences in the primary outcomes if the true differences are in the range of the minimum detectable differences. These scores were calculated based on the standard deviations reported by Kasmel and Tanggaard [38].

**Table 4 Tab4:** Minimum detectable differences (MDD) in primary outcome variables

Minimum Detectable Difference (MDD) and Percent Minimum Detectible Difference (%MDD)			
Estimated *n* = 144	$$\:\underset{\_}{x}$$ ^*^	SD^*^	MDD (%MDD)
Mobilization Scale (Total)	1.87	0.37	0.12 (6.5)
Participation Subscale	1.70	0.56	0.18 (10.9)
Motivation Subscale	1.83	0.56	0.18 (10.1)

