### Evaluator independence

An independent team from Virginia Tech’s Center for Public Health Practice and Research, separate from the academic team and community research teams, is responsible for the evaluation of the research project, including randomizing participants, collecting evaluation survey data, and assessing results. The evaluation team consists of a Principal Investigator trained in public health program evaluation, a project associate, and two graduate research assistants. All authors contributed to the evaluation plan, including team members responsible for planning and implementing the program. All team members will review and interpret the findings.

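### In the two SEED counties, counting strategy domains per group sets lists from 8 people against lists from 24, so the diversity comparison can reflect how the lists are partitioned

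*Protocol article*

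**What the plan says.** Strategy development (number, type and diversity) is among the secondary outcomes in Outcomes measures and is called a second outcome measure in Evaluation activities. The hypothesis under Research questions is that more engagement yields more diverse proposals. One measuring rule is given: each strategy is coded to a domain, and the codes are used to "calculate the number of domains addressed by each group and the number of domains (if any) that were unique to that group".

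The unit that produces a list differs by arm. Under Implementation, in SEED "each Topic group will work independently and develop its own set of priority strategies". Those sets are brought together for action planning; nothing says that they are brought together for the outcome. Delphi participants jointly produce one set. For the controls, "Control groups in each county will work separately, resulting in one set of strategies for each county". Table 3 plans three groups of 8 in each SEED county, one Delphi group of 24, and 24 controls in every county. Recruitment adds that the controls are drawn equally from the stakeholder groups.

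On coding, Evaluation activities says that "members of the research team will code the strategies". Evaluator independence describes a team, separate from the academic and community research teams, that "is responsible for the evaluation of the research project, including randomizing participants, collecting evaluation survey data, and assessing results". The Discussion says that this independent team collects and analyses the data.

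**The concern.** The number of distinct topics on a list rises with the number of people who contribute to it and with the number of entries it may hold, whatever the method. In the SEED counties the rule, taken at its word, sets a list from 8 people against one from 24 people of mixed background. The count of unique domains has a further asymmetry: a domain raised by two Topic groups of the same county is unique to neither, whereas the control has a single list and cannot lose a domain to another control list in its county.

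At stake is the diversity part of the stated hypothesis, for SEED against control and for SEED against Delphi. If the unit is left open, the sign of the SEED comparison can depend on whether the three lists are counted singly or together.

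**Working it through.** **Inputs.** The article gives no sample size, effect size or expected count for this outcome, so there is no figure to reproduce. Its planned numbers agree with each other: 3 × 8 = 24 per SEED intervention arm and 3 × (24 + 24) = 144 in total.

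| County and arm | Lists | People per list |
|---|---|---|
| SEED, intervention | 3 | 8 |
| SEED, control | 1 | 24 |
| Delphi, intervention | 1 | 24 |
| Delphi, control | 1 | 24 |

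**Step 1: effect of size alone.** Suppose that both arms behave identically. Each of *n* people proposes *s* strategies, and each strategy falls in domain *j* with probability *p_j*, for *D* domains in all. Then

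expected domains covered = Σ_j [1 − (1 − p_j)^(n·s)].

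*D*, *s* and *p_j* are assumptions: *D* = 8, 12 or 20; *s* = 1, 2, 3 or 5; domain frequencies equal or proportional to 1/rank.

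- Largest gap: *D* = 20, *s* = 1, equal frequencies. For 8 people, 20 × (1 − 0.95^8) = 6.73. For 24 people, 20 × (1 − 0.95^24) = 14.16. Ratio 0.48.
- Smallest gap: *D* = 8, *s* = 5, equal frequencies. For 8 people, 8 × (1 − 0.875^40) = 7.96. For 24 people, 8.00. Ratio 1.00.
- Middle case, *D* = 12 with 1/rank frequencies:

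| Strategies per person | 8 people | 24 people | Ratio |
|---|---|---|---|
| 1 | 5.05 | 8.74 | 0.58 |
| 2 | 7.35 | 10.73 | 0.68 |
| 3 | 8.74 | 11.46 | 0.76 |
| 5 | 10.29 | 11.89 | 0.87 |

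A second model, in which each person raises each of 20 domains with probability *p*, gives 20 × [1 − (1 − p)^n]: 6.7 v 14.2 at *p* = 0.05, 11.4 v 18.4 at 0.10, 16.6 v 19.9 at 0.20 and 18.8 v 20.0 at 0.30. Under both models the gap closes as the domains saturate.

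**Step 2: unique domains.** For three Topic groups and one control list, with *D* = 12 and 1/rank frequencies (20,000 simulated counties), the expected number of unique domains per Topic group v control is 0.45 v 1.99 at *s* = 1, 0.17 v 1.02 at *s* = 2 and 0.06 v 0.49 at *s* = 3.

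**Step 3: pooling.** If all proposals of the three Topic groups are pooled, both arms have 24·s draws and the ratio is 1.00 by construction. If instead each list is cut to *L* priorities, the pooled SEED arm has 3L draws against L. With *D* = 12 and 1/rank frequencies, pooled v single is 7.13 v 3.72 at *L* = 5, 8.74 v 5.05 at *L* = 8 and 9.46 v 5.76 at *L* = 10. The error now favours SEED.

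**Step 4: who codes.** Evaluation activities gives coding to an undefined research team. Evaluator independence and the Discussion give assessment and analysis to the independent team, which the article elsewhere (Randomization, Implementation) calls the evaluation team. The domain codes are the data for this outcome, so the statements need to be reconciled.

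**The case against.** The best reply is that *group* may mean arm. Research questions contrasts intervention and control groups, Recruitment speaks of an intervention group of 24, and the Discussion compares three methods. On that reading the comparison is already 24 against 24. This stands as far as it goes: the text permits it. But the text does not fix it, pooling is stated only for action planning, and the arm reading does not remove the error in Step 3 if prioritised lists are used.

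The model is also a simplification. A SEED list comes from seven facilitated meetings with conceptual modelling and focus group data; it is not the union of independent ideas. That stands too, so the figures show what size alone could do and do not forecast the trial's result. Separate Topic groups are part of the SEED Method, and counts for each are a fair description. That also stands, as description.

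A reader might infer that the whole second outcome is driven by group size. The documents do not support this: in the Delphi county both arms have 24 people and one list, and in the SEED counties the effect runs from negligible to about twofold on assumed inputs. A reader might also infer that the SEED developers will code with knowledge of the arm and so bias the result. The article neither defines the research team nor says that coders are unmasked, and masking is a detail that an article may leave to the full protocol.

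**Conclusion.** The point holds for the SEED comparisons. The counting rule is stated rather than merely left out, and followed literally it mixes the method with group size and number of lists. With no method effect, a Topic group of 8 covers 0.48 to 1.00 times the domains of a group of 24 over the scenarios in Step 1. These rest on assumed numbers of domains and of strategies per person, and on independent contributions. Counting per Topic group works against SEED; pooling fixed-length prioritised lists works for it. So the sign can depend on a choice that the article leaves open.

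Delphi against its own control is not affected, nor is the primary outcome, the Mobilization Scale total. The article describes counts without a decision rule, so one cannot say that the hypothesis would be accepted or rejected on this ground. On coding, the supportable point is narrower: two descriptions of who does the work need to be reconciled. The change should be made, but the trial's main result does not hang on it.

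**What to change.** 1. Make county by arm the unit of comparison, giving three county pairs.
2. In each SEED county, pool the three Topic-group lists and remove duplicates, then compare with that county's control list at the same stage. Use either all proposed strategies or, for prioritised lists, a common list length or rarefaction to an equal number of strategies. For a list of *N* strategies with *N_j* in domain *j*, rarefaction to *m* gives Σ_j [1 − C(N − N_j, m)/C(N, m)], with *m* the length of the shorter list in the pair. This also covers unequal recruitment, since Recruitment treats 24 per arm as a target.
3. Define a unique domain as one present in one arm of a county and absent from the other.
4. Keep Topic-group counts as description.
5. State that the existing independent evaluation team codes the strategies, from one shuffled list with arm, county and group labels removed, and align Evaluation activities with Evaluator independence and the Discussion.

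The cost is a few sentences and minor spreadsheet work, with no new staff or data. What is given up is inference at Topic-group level, since those counts become descriptive only.
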